# Evaluation of Tai Chi Yunshou exercises on community-based stroke patients with balance dysfunction: a study protocol of a cluster randomized controlled trial

**DOI:** 10.1186/s12906-015-0555-1

**Published:** 2015-02-25

**Keywords:** Tai Chi Yunshou exercises, Balance dysfunction after stroke, Community patients, Cluster randomized controlled trial

## Abstract

**Background:**

Balance dysfunction after stroke limits patients’ general function and participation in daily life. Previous researches have suggested that Tai Chi exercise could offer a positive improvement in older individuals’ balance function and reduce the risk of falls. But convincing evidence for the effectiveness of enhancing balance function after stroke with Tai Chi exercise is still inadequate. Considering the difficulties for stroke patients to complete the whole exercise, the current trial evaluates the benefit of Tai Chi Yunshou exercise for patients with balance dysfunction after stroke through a cluster randomization, parallel-controlled design.

**Methods/Design:**

A single-blind, cluster-randomized, parallel-controlled trial will be conducted. A total of 10 community health centers (5 per arm) will be selected and randomly allocated into Tai Chi Yunshou exercise group or balance rehabilitation training group. Each community health centers will be asked to enroll 25 eligible patients into the trial. 60 minutes per each session, 1 session per day, 5 times per week and the total training round is 12 weeks. Primary and secondary outcomes will be measured at baseline and 4-weeks, 8-weeks, 12-weeks, 6-week follow-up, 12-week follow-up after randomization. Safety and economic evaluation will also be assessed.

**Discussion:**

This protocol aims to evaluate the effectiveness of Tai Chi Yunshou exercise for the balance function of patients after stroke. If the outcome is positive, this project will provide an appropriate and economic balance rehabilitation technology for community-based stroke patients.

**Trial registration:**

Chinese Clinical Trial Registry: ChiCTR-TRC-13003641. Registration date: 22 August, 2013 http://www.chictr.org/usercenter/project/listbycreater.aspx.

## Background

Numerous people have problems with balance during movement and gait activities after stroke. Balance dysfunction often persists after acute stage, not only limiting general function but also participation in daily life. Among home-dwelling individuals with chronic stroke, balance problems have been identified as the strongest predictor of falling, especially during performance of complex tasks [1]. Previous studies have reported that poor balance has made a considerable contribution to history of multiple falls among individuals with chronic stroke [2]. In consequence, fear of falling may lead to reduced activity and sedentary lifestyle, which further disrupt function and health status (the vicious cycle of disability) [3].

An important emphasis in rehabilitation for people with chronic stroke is to improve balance and mobility function. In the acute stage post stroke, balance training programs include standing balance practice [4], group therapy [5], “patient-centered approach” (wherein participants chose the treatment method) [6], “motor relearning program”(intended to reinforce the relationship between training and functional performance) [7], intensive training versus patient initiated training [8,9], and conventional gait and balance training versus body weight–supported training [10]. For individuals in the subacute stage and chronic stage, there are group exercise therapy and balance exercise in one-on-one sessions [11]. Moderate evidence have suggested that balance performance can be improved following individual, one-on-one balance training for participants in the acute stage of stroke, and either one-on-one balance training or group therapy for participants with subacute or chronic stroke [11]. But stroke sufferers can ordinarily seek above treatment in high-grade hospitals, other than community health centers (CHCs). Exercise progression and instruction, supervision by health care professionals are required. Self-practice of stroke survivors is unfeasible. As a result, the direct and indirect health-care costs associated with stroke rehabilitation has become a main economic burden to patients. A majority of patients abandon rehabilitation after discharge in China, and their quality of life will become progressively worse. A more convenient, effective, simple and inexpensive approach of rehabilitation is eagerly needed for patients with balance dysfunction post stroke in communities.

Tai Chi, originated in China, is a martial art. As a mind-body practice, it combines meditation with slow, gentle, graceful movements, as well as deep breathing and relaxation, to move vital energy (or qi) throughout the body [12]. It is considered a complex, multicomponent intervention which integrates physical, psychosocial, emotional, spiritual, and behavioral elements [13]. The whole process emphasize smooth trunk rotation and coordination between the body and extremities [14,15]. It is thought to increase awareness of body alignment during movement by focusing on the placement of the feet, an upright position of the head and trunk, and the intentional, attentive body movement in the direction of the specific postures while Tai Chi practicing [16]. Furthermore, several scientific studies of Tai Chi have reported improvements in lower extremity range of motion [17], strength [17], and proprioception [18], as well as in controlling stepping strategies of the swing leg during gait [19], and enhanced neuromuscular responses involved in controlling the ankle joint during perturbations [20].

A large number of researches have showed that Tai Chi is an economic and effective exercise program for improving balance and balance confidence in older adults. Tai Chi practitioners are able to manage the techniques and do the exercise by themselves, without any help from medical equipments. Investigators have shown that long-term practice of Tai Chi can reduce the risk of falls [21,22]. Even intensive daily Tai Chi practice for 4 weeks can be sufficient to improve the standing balance in healthy elderly subjects [23]. Former studies also demonstrated that experienced Tai Chi practicers had better knee joint proprioception and standing balance than control subjects similar in age and activity level [24,25]. People who practiced Tai Chi have presented improved control of voluntary weight-shifting, better balance in perturbed stance under visual- or vestibular-challenged conditions, as well as better balance in perturbed single-leg stance [25].

There is less study on Tai Chi improving balance function after stroke, due to the great difficulty of completing the whole session of Tai Chi exercise for post stroke patients. Tai Chi Yunshou exercise , which is also called the “mother form”, is the basic technology form of Tai Chi. The exercise is composed of motion components effective for improving balance control such as knee flexion, body squat, transfer of positions and weight shifting. Furthermore, this exercise is easy to handle. Therefore, we hypothesized that Tai Chi Yunshou exercise may enhance the balance function of patients after stroke and ran a single-blind, cluster-randomized, parallel-controlled trial to confirm it. A cluster-randomized design was chosen over individual patient randomization in order to avoid intervention contamination and logistic complications within the CHCs. The work reported in this article is financed by the Special Scientific Research Fund of Public Welfare Profession of China (Grant No. 201307004), Ministry of Science and Technology and Ministry of Finance of the People’s Republic of China.

## Methods/Design

### Trial design

The effect of Tai Chi Yunshou exercises for stroke patients will be assessed in a single-blind, cluster-randomized, parallel-controlled trial. Patients will be recruited from multicenter CHCs outpatient clinics. The protocol will be conducted at CHCs run by the Rehabilitation Hospital affiliated to Fujian University of Traditional Chinese Medicine (Fujian province, China), the First Affiliated Hospital of Henan University of TCM (Henan province, China) and the Second Affiliated Hospital of Shandong University of Traditional Chinese Medicine (Shandong province, China). Fujian University of Traditional Chinese Medicine (FJTCM) is responsible for training and supervising investigators in all research centers. A total of 10 community health centers (5 per arm) will be selected and randomly allocated into Tai Chi Yunshou exercise group or balance rehabilitation training group. Each community health centers will be asked to enroll 25 eligible patients into the trial. Primary and secondary outcomes will be measured at baseline and 4-weeks, 8-weeks, 12-weeks, 6-week follow-up , 12-week follow-up after randomization. A flow diagram of this trial is shown in Figure 1.

**Figure 1 Fig1:**
[figure not shown]
**Study flow chart.**

### Ethical issues

Ethical approvals have already been granted by ethics committees in all research centers, including the ethics committee of The Rehabilitation Hospital affiliated to Fujian University of Traditional Chinese Medicine (2013KY-006-01, approval received in July 2013), the ethics committee of The First Affiliated Hospital of Henan University of TCM (2014HL010, approval received in March 2014) and the ethics committee of The Second Affiliated Hospital of Shandong University of Traditional Chinese Medicine (2013KY-006-01, approval received in March 2014). All participants will be fully informed about the protocol and sign the informed consent form prior to participation.

### Sample size

The sample size calculation is based on a comparison between the intervention group and the control group, represented by the improvement of the Berg Balance Scale (BBS) as the main effect indicators. Our preliminary test data indicated that the means with standard deviation of the score with the intervention group was 8.5 points and 2.8 points, while 6.5 points and 3.33 points with the control group. The number of qualified participants recruited from each CHC will not be less than 25. And prior data indicate that the intra-CHC correlation coefficient is likely to be, at most, 0.05. One hundred and fourteen individuals per group are calculated according to the formula [26]:$$ n=\frac{2\left[{\left({\mu}_{\alpha }+{\mu}_{\beta}\right)}^2{\sigma}^2\right]}{\delta^2}\left[1+\left(m-1\right)\rho \right] $$with a type I error of 5% (α = 0.05) and 90% power (β = 0.10). Assuming a dropout rate of 10%, the sample size is 125 for each group and 250 in the two groups. Therefore, in order to achieve 80% power with an average cluster size of 25 patients and ICC of 0.05, 10 CHCs will be required (5 per arm).

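### The sample-size paragraph claims both 90% and 80% power for the same 10 CHCs; with 5 clusters per arm, power at the planning ICC is about 84%

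*Protocol article*

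**What the plan says.** The Sample size section takes pilot data on BBS improvement: "the means with standard deviation of the score with the intervention group was 8.5 points and 2.8 points". For the comparison arm it gives a mean of 6.5 and an SD of 3.33. On cluster size it says "The number of qualified participants recruited from each CHC will not be less than 25", and it describes an intra-CHC correlation of 0.05 as a ceiling.

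It puts these into a two-mean formula with a design effect, "with a type I error of 5% (α = 0.05) and 90% power (β = 0.10", and reports the result: "One hundred and fourteen individuals per group are calculated according to the formula". It then inflates for dropout: "Assuming a dropout rate of 10%, the sample size is 125 for each group and 250 in the two groups". The closing sentence gives a different power for the same design: "Therefore, in order to achieve 80% power with an average cluster size of 25 patients and ICC of 0.05, 10 CHCs will be required".

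Neither the formula nor the text adjusts for the number of clusters. Under Statistical analysis, the primary comparison is the proportion of patients improved, in a mixed-effects logistic model with CHC as a random effect and adjustment for cluster-level variables. Continuous outcomes follow the same scheme in linear models.

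**The concern.** There are two faults. First, one set of inputs and one number of CHCs are given two powers, with design type II errors of 10% and 20%. Both figures are printed, so condensation into an article does not explain the conflict.

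Second, the formula uses normal quantiles. That suits a trial with many independent units, but here treatment is allocated to 10 CHCs. A contrast between two sets of 5 clusters has 2(5 − 1) = 8 degrees of freedom, with a critical value of 2.306 instead of 1.960. The design effect accounts for correlation within CHCs. It does not account for estimating the between-CHC variation from so few of them.

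The comparator is active balance training, so a null result is a realistic outcome and readers will turn to the stated power to interpret it. As printed, they cannot tell which figure the sponsor stands behind, and the higher one is too high at the planning ICC.

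**Working it through.** **Inputs (Sample size section).** Difference δ = 8.5 − 6.5 = 2.0. Pooled variance = (2.8² + 3.33²)/2 = 9.464, so SD = 3.076. Cluster size m = 25; ICC ρ = 0.05; design effect = 1 + 24 × 0.05 = 2.2. Clusters k = 5 per arm; dropout 10%. The section does not say whether α = 0.05 is one- or two-sided. I take two-sided, because one-sided gives only about 90 per group.

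**Step 1: the plan's own figure.** n = 2(z₁₋α/₂ + z₁₋β)²σ²/δ² × [1 + (m − 1)ρ].

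- At 90% power: 2 × (1.960 + 1.2816)² × 9.464/4 = 49.72; × 2.2 = 109.4, so 110 per group.
- At 80% power: 2 × (1.960 + 0.8416)² × 9.464/4 = 37.14; × 2.2 = 81.7, so 82 per group.

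The stated 114 is close to the first and far from the second. A t-based individual sample size of 51 gives 51 × 2.2 = 112.2, or 113, so 114 is a 90%-power figure within ordinary rounding. At 80% power, 82/0.9 is about 92 per group, or 4 CHCs of 25 per arm. The closing sentence's 80% therefore does not produce 5 per arm.

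**Step 2: power with 5 clusters per arm.** SE = σ√{2[1 + (m − 1)ρ]/(km)}. The non-centrality is δ/SE, and power is taken from the non-central t on 8 df at 2.306.

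- No dropout, m = 25: SE = 3.076 × √(2 × 2.2/125) = 0.577; non-centrality 3.465; power 85.7%.
- 10% dropout, m = 22.5: design effect = 1 + 21.5 × 0.05 = 2.075; SE = 3.076 × √(2 × 2.075/112.5) = 0.591; non-centrality 3.385; power 84.1%.

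With 1.960 and normal quantiles, the same two cases give 93.4% and 92.3%.

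**Step 3: sensitivity to the ICC** (8 df, m = 22.5).

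| ICC | Power |
|---|---|
| 0.05 | 84.1% |
| 0.04 | 87.8% |
| 0.03 | 91.3% |
| 0.02 | 94.5% |

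**Step 4: sensitivity to cluster-level adjustment** (ICC 0.05, m = 22.5). Each cluster-level covariate costs one degree of freedom: 82.6% on 7 df and 80.4% on 6 df. These figures allow for the lost degrees of freedom only, not for any variance the covariate explains.

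**The case against.** **The ICC is a ceiling.** The section presents 0.05 as the most the correlation is likely to be, so 84% is the power at the unfavourable end of the sponsor's expectation. This stands, and the claim must be tied to that ICC. A reader might infer that the trial cannot reach 90% power at all; the documents do not support that, since an ICC of about 0.03 gives it. But 0.05 is the value the plan used in its formula and repeated in its conclusion, so it is the right one for checking the claim.

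**84% is above 80%.** True: the shortfall is against the 90% statement only. The design meets the lower figure for the continuous comparison, and there is no case for calling the trial too small on that account.

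**The arithmetic slips.** A reader might count 114 (formula: 110) and 125 (114/0.9 = 127) as further errors that weaken the design. They do not. The first gap is small and on the cautious side. On the second, 125 enrolled leaves 112.5 evaluable, still above 110. Both are minor notes without consequence.

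**The 5.8-point figure.** A reader might turn the 5.8-point change under Primary outcome into a larger SD and a much lower power. That needs a multiplier and a study population that the document does not give. The trial's own pilot SDs are the relevant inputs.

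**The test could use normal quantiles.** The article states no degrees-of-freedom method. A z reference would show about 92% nominal power, but comparing a statistic on 8 df with 1.960 gives a two-sided type I error of about 8.6%. The stated 5% would then fail instead.

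**84% is not the power of the primary analysis.** This also stands. The calculation concerns mean BBS improvement, whereas the primary analysis is a responder comparison by logistic model. Any restated figure must say so.

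**Conclusion.** Wrong as written. The section gives two powers for one design, and only 90% agrees with its 114, 125 and 5 CHCs per arm. At the plan's own inputs that 90% is not reached: power is about 84% with 10% dropout and about 86% without, so the type II error is about 16% or 14% instead of 10%. The normal-quantile formula overstates power by about 8 percentage points (92.3% against 84.1%, and 93.4% against 85.7%).

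This rests on a difference of 2.0, a pooled SD of 3.08, ICC 0.05, a two-sided 5% test, equal cluster sizes and 8 degrees of freedom. It applies to the continuous BBS improvement only and shrinks as the ICC falls below its stated ceiling. It is a fault in the stated power. It does not show that the number of CHCs or patients must change.

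**What to change.** Delete the conflicting 90% and 80% statements and give one figure with its conditions. For example: power is about 84% to detect a 2.0-point difference in mean BBS improvement (SD 3.08) at ICC 0.05, with 5 CHCs per arm, about 22 evaluable patients per CHC, and a two-sided 5% t reference on 8 degrees of freedom.

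Add three short notes:

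- The ICC is an upper bound; power is 87.8% at 0.04 and 91.3% at 0.03.
- Each cluster-level covariate lowers the figure, to about 83% on 7 df and 80% on 6 df at ICC 0.05.
- The figure is not the power of the logistic responder analysis named as primary under Statistical analysis.

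While editing, the authors may state that the formula itself gives about 110 per group and that 125 enrolled leaves about 112 evaluable.

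The cost is one rewritten paragraph and a less favourable stated power than 90%. Enrolment and the number of CHCs stay as they are.

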### Participants and recruitment

CHC recruitment will commence with an initial letter mailed out to the directors, requesting that the directors contact the research coordinator for further information related to the study if they are interested in taking part. CHCs able to complete the task within the specified time are eligible for enrollment at cluster level. Prior to implementation, a meeting will be held with the directors of eligible CHCs to share objectives and the scope of the study, obtaining their agreement for the trial to be undertaken in their work unit.

Outpatients with balance dysfunction after stroke will be recruited from CHCs. We will screen the eligible participants by means of newspaper publicity or posting up posters, sending leaflets and referrals from neurologists or physical therapists. The potential eligible patients who are interested in this study can contact with recruiters directly. Suitable individuals should be in according with the inclusion criteria and not meeting the exclusion criteria. All participants will be required to provide informed consent prior to participation.

### Inclusion criteria

For inclusion, participants should fulfilled all following:A clinical diagnosis of stroke according to the criteria regulated by the Fourth National Cerebral Vascular Disease Conference [27], confirmed by CT or MRI;Clinically first ever stroke > 3 months;Be aged 45 to 75 years;Manifestation of balance dysfunction;Ability to walk at least 6 meters with or without aids;Agreement of patient or his/her legal guardian and signed informed consent form. Able to understand, implement rehabilitation training.

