### Randomization and allocation concealment

Participating CHCs are randomly assigned to either the intervention or the control arm by a 1:1 ratio. Random allocation sequence will be produced by an independent statistician via the PLAN sentences of the statistical software SAS 8.2, who works in the Evidence-Based Center of FJTCM. The randomization program of CHCs will be managed by a specified project manager who is not involved in the recruitment program of this trail, and be concealed to the screeners and outcome assessors. Randomization into the Tai Chi Yunshou exercises training is based on the CHC in which the patient lives. Study objectives, intervention, and data assessment pertain to the individual patient level.

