**Table 1 Tab1:** **Baseline descriptive data**

**Data**	**Content**
General data	CHC in which patients are recruited from, the date screening, patient’s address, name of accompanying, family members or the patient’s telephone number
Demographic data of subject	Gender, age, height ,weight, nationality, level of education and profession
Assessment of balance function before test	The ability to stand independently or with auxiliary, how many metres could walk with or without aids
Other	Previous treatment and duration of stroke, injury site of cerebrum, type of stroke and number of stroke

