### Statistical analysis

The data will be analyzed at the patient level by a statistician working in the Center of Evidence-based Medicine of FJTCM, who is not involved in this trial. The primary analysis will compare the proportion of patients improved of balance function at the 12-week after treatment using a mixed-effects logistic regression model in the intention-to-treat sample (including all randomized patients). Treatment condition (intervention versus control) will be treated as a fixed effect. Baseline severity of balance dysfunction will be included as a covariate and variation among patient clusters (recruited by the same CHCs) will be modeled through random effects. Potential confounding for other measured cluster-level variables such as population size will be adjusted. Continuous outcomes will be analyzed according to the same scheme, but in linear rather than logistic regression models. Item-level missing data in psychometrically sound instruments will be treated in compliance with the corresponding manuals. If no recommendations are available, the expectation-maximization (EM) algorithm will be used to impute up to 30% of missing item responses. Unit-level missing data (patients not providing data for a whole measurement point due to dropping out of the study, for example) will be imputed via the EM algorithm using existing information from the baseline assessments. Further secondary analyses will include analyses in the per-protocol (completer) sample to test the robustness of the primary findings. No interim analysis is planned. Intervention-related data are stored and analyzed separately. All analyses will be implemented using SAS software (version 8.2, SAS Institute, Cary, NC, USA).

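### Time since stroke is recorded at baseline and plausibly prognostic, but the stated model does not name it as a covariate; adding it would gain precision at almost no cost

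*Protocol article*

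**What the plan says.** The Inclusion criteria of the protocol article require "Clinically first ever stroke > 3 months" and set no upper limit. Table 1 lists, among the baseline data, "Previous treatment and duration of stroke, injury site of cerebrum, type of stroke and number of stroke", so time since stroke will be in the database.

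Under Randomization and allocation concealment, "Participating CHCs are randomly assigned to either the intervention or the control arm by a 1:1 ratio". There are 5 CHCs per arm, and no stratification or matching is stated.

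The Statistical analysis section gives the terms of the primary mixed-effects logistic model. Treatment is a fixed effect. At patient level, "Baseline severity of balance dysfunction will be included as a covariate". For clustering, "variation among patient clusters (recruited by the same CHCs) will be modeled through random effects". It then adds: "Potential confounding for other measured cluster-level variables such as population size will be adjusted". Continuous outcomes follow the same scheme in linear models. Time since stroke is named neither in the randomization nor in the model.

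**The concern.** The primary outcome is the proportion of patients improved at 12 weeks, and the sample size is built on BBS improvement. How much a patient improves over 12 weeks may depend on how long ago the stroke occurred. Two patients with the same baseline BBS, one at 4 months and one at 5 years, may be on different courses. That is a clinical inference, but the Background itself distinguishes acute, subacute and chronic stages. Baseline severity may therefore leave part of the prognostic information unused.

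With ten randomized units and no stratification, the arms can easily end up with different mixes of recent and old strokes. The stake is twofold. Avoidable between-CHC variation stays in the error of the treatment comparison. A visible imbalance in the baseline table would also invite doubt about the result that an unadjusted model cannot answer. The section names a cluster-level covariate, population size, which must be estimated from only 10 units. It does not name this patient-level variable, which is already collected.

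**Working it through.** **Inputs from the Sample size section.** Improvement in BBS 8.5 (SD 2.8) versus 6.5 (SD 3.33); intra-CHC correlation (ICC) 0.05; 25 patients per CHC; 125 per group after dropout. Two-sided alpha is assumed, since sidedness is not stated.

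**Reproducing the plan's own figure.**
- Pooled variance = (2.8² + 3.33²)/2 = 9.46, so SD = 3.076. The difference is 2.0.
- Design effect = 1 + 24 × 0.05 = 2.2.
- The printed normal formula at 90% power gives 49.7 × 2.2 = 109.4, so 110. The t-test variant gives 51 × 2.2 = 112.2, so 113. With the SD rounded to 3.1, the t-test variant gives 52 × 2.2 = 114.4. The stated 114 per group is therefore reproduced closely.
- 114 × 1.1 = 125.4, matching the stated 125.

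**Planned standard error of the BBS difference.** √(9.46 × 2/125 × 2.2) = √0.333 = 0.58 points. Its 95% range is ±1.96 × 0.58, about ±1.1 points.

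**Assumed inputs, not in the documents.** Recent strokes gain D = 2 to 3 BBS points more over 12 weeks than older ones. The share of recent strokes varies between CHCs with SD s = 0.10 to 0.20.

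**SD of the chance arm difference due to stage mix** = D × s × √(2/5), with √(2/5) = 0.632.
- Low: 2 × 0.10 × 0.632 = 0.13.
- High: 3 × 0.20 × 0.632 = 0.38.

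**Standard error if that component is removed.**
- Low: √(0.333 − 0.016) = 0.563, and 0.563/0.577 = 0.976, about 2% lower.
- High: √(0.333 − 0.144) = 0.435, and 0.435/0.577 = 0.754, about 25% lower.

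This assumes that baseline BBS absorbs none of the stage effect and that the total ICC stays at 0.05. It counts only the between-CHC part.

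**Comparison with the planned clustering allowance.** ICC 0.05 allows a between-CHC variance of 0.05 × 9.46 = 0.47. Stage mix would contribute (2 × 0.10)² = 0.04 to (3 × 0.20)² = 0.36, that is 8% to 76% of the allowance. It stays inside the allowance throughout, but the upper end would leave little room for other site differences.

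**Second set of assumptions.** Take a share p of recent strokes of 20% to 50%, an ICC of that share of 0 to 0.2, and D = 1 to 3. The 95% range is ±1.96 × D × √(2p(1 − p)(1 + 24 × ICC)/125).
- Low: 1.96 × 1 × 0.051 = 0.1.
- High: 1.96 × 3 × 0.152 = 0.9.

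Both lie within the ±1.1 points above.

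**Limit of the calculation.** It is on the BBS scale. In a logistic model, adjusting for a prognostic covariate also changes the conditional odds ratio, so the gain appears as power and not necessarily as a smaller standard error of the log odds ratio. The 2% to 25% applies directly to the linear models only.

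**The case against.** The strongest reply is that nothing here is an error. A broad entry rule is legitimate in a community trial. Chance imbalance between randomized CHCs is sampling error, which the design effect and the random CHC effect exist to carry. Baseline severity may already absorb part of the stage effect. The article condenses a fuller plan that may name more covariates. The size rests on assumed inputs, and the same argument could add stroke type or lesion site.

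Most of this stands, and it rules out several stronger readings that a reader might infer:
- **That the trial would mistake a stage imbalance for an effect of the exercise.** The imbalance is not systematic, and on every assumption tried it falls within the error already planned for.
- **That the entry rule conflicts with the rationale.** The Background does say "An important emphasis in rehabilitation for people with chronic stroke is to improve balance and mobility function", but it also covers earlier patients: "For individuals in the subacute stage and chronic stage, there are group exercise therapy and balance exercise in one-on-one sessions". The stated aim concerns patients after stroke generally.
- **That CHCs recruit by different routes.** Participants and recruitment lists one common set of routes for the whole trial and does not say that they vary by CHC.
- **That time since stroke will not be used.** The supportable wording is that the model does not name it.

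What the reply does not remove is the gain. The article states the model's terms, and its open list covers cluster-level variables only, so a patient-level variable does not naturally fall under it. The random effect widens the interval to allow for imbalance; a prognostic covariate can recover some of that precision and adjust for the imbalance that actually occurs.

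**Conclusion.** The point holds as a near-costless improvement to a stated model. It is not a source of bias, and the entry rule is not at fault. Time since stroke is collected, plausibly prognostic for 12-week improvement, and free to differ between 5 unstratified CHCs per arm. On the assumptions of a 2 to 3 point gain difference and a between-CHC SD of share of 0.10 to 0.20, the imbalance has SD 0.13 to 0.38 BBS points against a planned standard error of about 0.58, and adjustment would lower that error by roughly 2% to 25%. The upper figure needs stage mix alone to make up about three quarters of the planned between-CHC variance, so it is an outer bound for these assumptions. If baseline BBS carries part of the stage effect, the gain is smaller. The documents supply neither the stage mix nor the gain by stage, so the true size cannot be fixed from them.

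**What to change.** In the Statistical analysis section, name time since stroke at baseline as a prespecified patient-level covariate next to baseline BBS, in the primary logistic model and in the linear models. A continuous form such as log months avoids choosing a stage cut-off, which the article does not give. Make sure that the duration of stroke in Table 1 is recorded precisely enough to compute months.

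The cost is one line of text and no new data. Because the variable is measured on patients, its slope is estimated largely within CHCs and uses essentially none of the 10 − 2 = 8 between-CHC degrees of freedom. Eligibility and the 125 per group are unchanged. Since recruitment had begun when the article was written, the change should be dated and documented before the allocation code is opened. Any presentation of results by stage is optional and descriptive only.
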